**Introduction**
Categories of riskAmputationDiabetes and your feet: nerves, blood vessels, skin, joints
**Inspection**
Visual inspectionFoot conditions—skin and nails 1 (corns and calluses)Foot conditions—skin and nails 2 (fissures or fungal nail and skin [tinea pedis] or dystrophic nail or ingrown toenails)Foot conditions—deformities 1 (claw toes or hammer toes or bunions)Foot conditions—deformities 2 (Charcot foot)Foot conditions—peripheral neuropathyFoot conditions—peripheral vascular diseaseOther foot conditions commonly encountered by patients with diabetesProfessional foot examination
**Prevention**
HygieneDiabetes-friendly footwearHow to trim nails safelySkin careSimple exercises for the foot or calfPractices to avoid
**Wound care**
Wound care—basicDiabetic foot ulcerWound care—diabetic foot ulcer

Concurrent with curriculum development, the team was working on identifying relevant app features and conceptualizing app mechanics with instructional experience as a focus to connect user flow between features and align it with desirable behavior changes. In total, 3 levels of learning adaptations have been devised: (1) personalization of the content based on the role served, (2) personalization of the order of the modules based on the user’s risk stratification identified in the onboarding process, and (3) personalization of the content based on user’s knowledge level through knowledge assessment. This personalization forms the basis of learning framework in Well Feet. Additional features such a Frequently Asked Question chatbot, meal diary, feet diary, medication reminders steps, and sleep tracker are further added to enhance user experience. Finally, the app includes an automated notification system which in case of inactivity prompts the user to use the app.

#### Setting

Due to the nature of the Well Feet intervention being an mHealth app, participants are anticipated to engage with the intervention at their own discretion. Nevertheless, this study’s team will remind the participants at the start of this study to engage with Well Feet app throughout this study’s period.

### Data Collection

#### Overview

The participant flow through this study is illustrated in Figure 2. Consenting participants will be assigned with a study ID that will be used as their coded identifier throughout this study. Participants will receive a briefing regarding this study’s procedures and will answer a baseline questionnaire using a digital survey platform, REDCap (Research Electronic Data Capture, Vanderbilt University), accessed through a provided tablet. A study ID will be assigned to each participant to keep their answers to the questionnaire anonymous. A research assistant will assist with participants to complete the prescreening and enrollment sections, that is, for the participant's details and eligibility form. The clinical research assistant will access and extract medical records to complete the section with medical and health related information. Participants will complete sociodemographic information and questionnaire sections by themselves. The research assistant may assist the participants if help is needed. Additionally, the research assistant will access and extract medical records to complete the section with medical and health related information. Carers will go through the same recruitment and briefing flow as the patients. However, no medical record will be extracted for carers. Completion of the questionnaire is on a voluntary basis. If the participant requests to fill out the questionnaire at their own convenience, the research assistant will send them a link to the questionnaire through their preferred communication medium. The research assistant will also follow-up with a gentle reminder to complete the questionnaire in a case the participant did not fill it out.

**Figure 2 figure2:**
[figure not shown]
Participant flow through this study (CONSORT [Consolidated Standards of Reporting Trials]).

The intervention will begin with the participants receiving the link to the app. The participants will be asked to use the app for up to 1 month. At the end of the period, they will be asked to fill out an end point questionnaire and will be invited to participate in focus group discussions or an interview, in case the participant cannot participate in focus group discussions, as a follow-up. To minimize attrition, prompts will be sent via the participants’ chosen mode of contact (eg, via email, telephone, SMS text message, or WhatsApp) to indicate it is time to complete the survey or participate in the focus group discussion.

#### Outcome Measures

This study’s outcomes of interest encompass methodological, procedural, and feasibility questions. Various factors are considered. Table 1 displays the primary outcomes including usability of the app and qualitative perspective on user experience. Multimedia Appendix 2 [37-43] displays secondary outcomes, including changes in foot care knowledge, self-management behaviors, and quality of life. Additionally, usage and learning analytics will be collected from the backend of the app.

**Table 1 table1:** Primary outcomes.

Outcome measure			Measure description		Time frame
**Primary outcome**					
	Usability of a health app among patients and carers at the end of the trial (1 month)	A validated questionnaire, MAUQ^a^ [44], will be used to determine the usefulness and applicability of an app with a conversational agent or chatbot among patients and carers. The questionnaire consists of 3 subscales, which are ease of use (5 items), interface and satisfaction (7 items), and usefulness (6 items). Participants rate each of the items using a 7-point Likert scale ranging from 1 (strongly disagree) to 7 (strongly agree). The usability of the app is determined by the total and average of all statements—the higher the overall average, the better the usability of the app. However, if the average score is lower than 4, it means that the usability of the app is not good. The MAUQ exhibited strong psychometric characteristics, as evidenced by an overall Cronbach α value of .914 [44].		End-of-trial (1 month)	
	Qualitative perspective on a conversational agent or chatbot app usage experience among patients and carers at the end of the trial (1 month).	A focus group discussion among the app users will be carried out to collect feedback on the user experience at the end of the trial. Qualitative data on app usability, app applicability, app relevance, and user feedback will be retrieved from the focus group discussion.		End-of-trial (1 month)	

^a^MAUQ: mHealth (mobile health) App Usability Questionnaire.

### Data Management

All data will be handled according to patient Nanyang Technological University data protection and privacy policy [45] as well as National Healthcare Group, Tan Tock Seng Hospital data protection and privacy policy [46] with all participants assigned a study ID to deidentify data and any personal information about participants will be stored separately from deidentified data. Data collected via digital survey platform, REDCap will be stored on secure servers at Center for Population Health Sciences, Lee Kong Chian School of Medicine, Nanyang Technological University. The data gathered through the app will be stored in a university-approved cloud server as a multiencrypted database with authorization granted for principal investigators and study team members to prevent unauthorized persons from accessing the data. All other physical forms will be stored in a locked filing cabinet in the clinical site and will be accessible only to the site-principal investigator and appointed research assistant. User’s interaction within the Well Feet app will be monitored to identify participants’ signaling their need for more extensive support.

### Ethical Considerations

This study was approved by the National Healthcare Group Domain Specific Review Board (2022/00614) and the Nanyang Technological University institutional review board (IRB-2023-157), ensuring that the welfare and rights of all participants is protected in this study. This study will be conducted in accordance to the Helsinki code of ethics ensuring that patients’ confidentiality, integrity, and vulnerability are kept throughout their participation. Informed consent will be collected to ensure participants are aware of this study’s procedure and their rights to withdraw from this study without the need to give any reason. Participants will be provided with contact information within the informed consent form should they have any concern regarding the conduct of the feasibility study.

### Analysis

#### Quantitative Analyses

The questionnaires answered by the participants will be summarized using descriptive statistics, and the data will be presented as frequencies, percentages for categorical variables and means, SDs, medians, and IQRs for continuous variables depending on the distribution of the variable. Descriptive statistics will also be used to assess measures of app usage. Differences between groups will be analyzed using chi-squared or Fisher exact test for nominal data and changes within the groups over time (pre-post) will be analyzed using the Wilcoxon signed rank test. R (R Core Team) and Stata (StataCorp) will be used for all analyses.

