#### Recruitment

Patients will be recruited through referrals from attending endocrinologists at Tan Tock Seng Hospital. Recruitment will take place during the patients’ routine clinic visits at Diabetes Clinic. The endocrinologists will screen for potential participants’ eligibility based on this study’s inclusion and exclusion criteria before referring them to the appointed research assistant to complete the recruitment process. At the same time, patients will be asked to nominate their carers to participate in this study. The nomination is optional and subject to patients’ and carers’ willingness. Notwithstanding, patients without a carer can still participate in this study. Potential patients and carers who choose not to participate in this study will be asked an open-ended question about the reasons. It will be highlighted that answering the question is voluntary. The information will be used to inform about the barriers to recruitment and acceptability of the intervention.

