### Sample Size and Power Calculation

Since this is a feasibility study, a formal sample size calculation is not required [34]. Our target is to recruit a minimum of 30 participants (with a maximum of 40), evenly divided into groups: persons living with diabetes and carers of persons living diabetes, with 15 participants in each group (with a maximum of 20). This approach is based on a previous study that shows a feasibility study requires 30 or more participants to estimate a parameter [35]. An arbitrary sample size of 30 would provide 0.75 (75%) power to detect a medium effect size of 0.5. Alternatively, a sample size of 40 would provide even greater power at 0.87 (87%).

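### The probable patient–carer pairing is ignored: the between-group tests lose power, and the stated power of 0.75/0.87 needs all participants pooled as independent

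*Protocol article*

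**What the plan says.** - **Source of carers.** Under Recruitment, endocrinologists refer patients at clinic visits, and "patients will be asked to nominate their carers to participate in this study". Nomination is optional, and a patient without a carer may still join. No other route for carers is described.
- **Group sizes.** Under Sample Size and Power Calculation: "Our target is to recruit a minimum of 30 participants (with a maximum of 40), evenly divided into groups", with 15 to 20 in each group. The groups are patients and carers. The Results section reports 40 enrolled but gives no split.
- **Power.** The same section states: "An arbitrary sample size of 30 would provide 0.75 (75%) power to detect a medium effect size of 0.5". For 40 participants it gives 0.87. It names no test, significance level or sidedness, and says that a formal calculation is not required.
- **Tests.** Under Quantitative Analyses: "Differences between groups will be analyzed using chi-squared or Fisher exact test for nominal data". Pre-post change is tested within the groups by the Wilcoxon signed rank test.

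The article nowhere mentions pairing, clustering or a matched analysis.

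**The concern.** A nominated carer and the nominating patient deal with the same feet and the same disease, and may use the app together. Their answers are likely to be positively correlated. Two statements in the plan take no account of this.

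First, chi-squared and Fisher tests compute the variance of a difference as if the two groups were unrelated. Positive correlation makes the true variance smaller, so these tests miss differences that a paired or clustered analysis could detect.

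Second, the power figures are quoted for the total of 30 or 40 people. If these form pairs, the total carries less information about a pooled mean than its count suggests. The planned pre-post tests also do not use that total, because they are run within each group.

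The article says that the findings will shape a later randomized trial. An optimistic power statement and an inefficient patient–carer comparison would be carried into that design.

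**Working it through.** **Inputs from the article:** N = 30 or 40 in total; 15 to 20 per group; standardised effect d = 0.5; stated power 0.75 and 0.87.

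**Assumptions:** two-sided 5% level (not stated); within-pair correlation ρ of 0.3 to 0.5; share s of participants who are in pairs, 1 or 0.5. The article gives neither ρ nor s.

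**1. Reproducing the stated power.** Paired t-test, noncentrality d√n, n − 1 degrees of freedom:
- n = 30: 0.5 × √30 = 2.74, power 0.754 (stated 0.75).
- n = 40: 0.5 × √40 = 3.16, power 0.869 (stated 0.87).

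Alternatives:

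| Variant | N=30 | N=40 |
|---|---|---|
| One-sided paired t | 0.848 | 0.928 |
| Normal approximation | 0.782 | 0.885 |
| Pooled signed rank, efficiency 0.955 | 0.733 | 0.853 |
| Two-sample t, 15 or 20 per group | 0.262 | 0.338 |

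The pooled signed rank version comes within 2 points but fits less well. Both versions that come close count every patient and carer as an independent unit in one pre-post test.

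**2. Allowing for pairs.** With sN/2 pairs, the variance of the pooled mean change is (σ²/N)(1 + sρ), so the effective N is N/(1 + sρ). Here ρ is the correlation of change scores within a pair.

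| N | s | ρ | Effective N | Power |
|---|---|---|---|---|
| 40 | 1 | 0.3 | 40/1.30 = 30.8 | 0.765 |
| 40 | 1 | 0.5 | 40/1.50 = 26.7 | 0.700 |
| 40 | 0.5 | 0.3 | 40/1.15 = 34.8 | 0.817 |
| 40 | 0.5 | 0.5 | 40/1.25 = 32.0 | 0.782 |
| 30 | 1 | 0.3 | 30/1.30 = 23.1 | 0.632 |
| 30 | 1 | 0.5 | 30/1.50 = 20.0 | 0.565 |

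**3. The pre-post tests actually planned.** Within one group, the same formula gives:
- n = 15: 0.5 × √15 = 1.94, power 0.438.
- n = 20: 0.5 × √20 = 2.24, power 0.565.

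With the signed rank efficiency of 0.955 these are 0.42 and 0.54. Pairing does not enter, because each group contains only one member of each pair (unless one patient has several carers).

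**4. The patient-versus-carer tests.** With 20 per group, the true variance of the difference in proportions is (1 − sρ) times the variance that an independent-samples test uses, where ρ is the correlation of the binary answers. The standard error used is therefore too large by the factor 1/√(1 − sρ):
- All paired: 1/√0.70 = 1.20 and 1/√0.50 = 1.41 for ρ = 0.3 and 0.5.
- Half paired: 1/√0.85 = 1.08 and 1/√0.75 = 1.15.

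Simulated rejection rates under no difference, 20 pairs, true rate 0.5, nominal 5%:

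| ρ (binary scale) | Chi-squared | Fisher |
|---|---|---|
| 0 | 4.4% | 2.2% |
| 0.3 | 1.9% | 0.7% |
| 0.5 | 0.5% | 0.1% |

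If ρ is instead placed on a latent normal scale, 0.3 and 0.5 correspond to binary correlations of (2/π)·arcsin(ρ) = 0.19 and 0.33 at a rate of 0.5. Chi-squared then rejects in about 2.6% and 1.5% with all paired, and 3.2% and 2.8% with half paired. On either scale the test is conservative.

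**The case against.** - **The pairing is inferred.** Nomination is optional, either party may decline, and the carer criteria ask for care of a patient with type 2 diabetes, not of an enrolled one. The article gives no pair count. This stands: one cannot claim that every carer is paired. Nomination is still the only route described and the groups are planned as equal, so substantial linkage is the likely case.
- **The planned tests give no false positives.** A reader might infer inflated type I error or intervals that are too narrow. The article does not support that. It plans no pooled significance test and no confidence intervals, and its pre-post tests are within groups. For chi-squared and Fisher the error is in the safe direction, and Fisher is already at 2.2% without any pairing.
- **The groups are not defined in the analysis section.** The Discussion also speaks of groups of users by usage pattern, for which a patient–carer matched test would not be the right one. This stands as a limit on scope. Patients and carers are the only groups that the Methods define.
- **It is a feasibility study.** Its primary outcomes are a usability score and focus groups, and a formal sample size calculation is disclaimed. This lowers the weight. It does not make the quoted power figures apply to the planned tests.

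**Conclusion.** The point holds in a limited form. Many or most carers are probably linked to an enrolled patient, and the plan takes no account of it. The consequences are:

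- Patient-versus-carer chi-squared and Fisher tests are conservative and lose power.
- The stated 0.87 at N=40 becomes about 0.77 to 0.70 with everyone paired, or 0.82 to 0.78 with half paired.
- Apart from pairing, the within-group tests that the plan names have only about 0.44 to 0.56.

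The ranges rest on an assumed correlation of 0.3 to 0.5, an assumed share of pairs, and a two-sided 5% level. The reproduction of 0.75 and 0.87 depends only on the last of these.

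The within-group Wilcoxon tests are sound in this respect. Nor should a reader assume that the linking variable is already in the data: the article describes individual study IDs only.

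**What to change.** 1. Record the patient–carer link or, as enrolment is complete, recover it from the nominations. Report the number of pairs.
2. For patient-versus-carer comparisons of nominal data, use a dyad-clustered method that keeps unpaired participants (GEE or a mixed model). With about 20 pairs at most, a small-sample correction is advisable. If all participants are paired, McNemar's test on complete dyads is enough. Keep chi-squared and Fisher for comparisons of unlinked groups.
3. If any pooled patient-plus-carer estimate is reported with inference, give a dyad-clustered interval.
4. Restate power per group (about 0.44 at n=15 and 0.56 at n=20 for d=0.5), or give the pooled figure as a range over plausible correlations, and name the test and significance level.

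The cost is one linking variable, slightly more analysis work and a less favourable power statement. No further participants are needed.

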#### Qualitative Analyses

All focus group discussions will be recorded on a digital teleconferencing platform (ie, Zoom; Zoom Video Communications, Inc), which will then be transcribed verbatim. Any identifiers in the transcriptions will be removed. Thematic analysis will be used to identify participants’ experience, overall acceptance, and feedback. The analysis of the responses will start immediately following the first focus group and transcription. Initial codes will be generated, then collated into themes to identify the key patterns and key themes of the focus group discussions using the procedures suggested by Clarke and Braun [47].

### Dissemination

This study’s findings will be published in an open access journal and via national and international conference presentations.

## Results

This study was funded in October 2019 and received ethics approval in February 2023. Recruitment of this study was done in July 2023 with 40 participants enrolled. Well Feet app is expected to be published at Google Play and iOS testflight at the end of August 2023, followed by a month-long intervention period. Analysis of results is expected to be completed by October 2023, and trial results are expected to be published in spring 2024.

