**Results:**

Patient recruitment began in July 2023, and the intervention and data collection will be completed by the end of September 2023. This study has been approved by National Healthcare Group Domain Specific Review Board (2022/00614) on February 10, 2023. The expected results will be published in spring 2024.

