### Intervention

#### Well Feet mHealth App

Well Feet is a diabetes and foot care education mHealth developed by Nanyang Technological University. The technical building process of the app is outsourced to a university-appointed vendor while the content building process was carried out in-house. The app was made available to download both for iOS and Android. Screenshots of Well Feet’s main interface and features are shown in Figure 1.

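### By the article's own calendar, most baseline questionnaires precede app access by about 1 to 2 months, so the pre-post secondary outcomes span about 2 to 3 months rather than the 1-month intervention

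*Protocol article*

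**What the plan says.** **Enrollment.** The main-text Results section says "Recruitment of this study was done in July 2023 with 40 participants enrolled". The abstract agrees on the start and gives the end: "Patient recruitment began in July 2023, and the intervention and data collection will be completed by the end of September 2023".

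**Baseline.** Under Data Collection (Overview), once consent is obtained, "Participants will receive a briefing regarding this study’s procedures and will answer a baseline questionnaire using a digital survey platform", on a tablet that the study provides. A participant who asks may instead receive a link and answer later, with reminders. No deadline is given, and nothing ties completion to the app's release.

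**Start of exposure.** The text after the Figure 2 caption says "The intervention will begin with the participants receiving the link to the app". The end point questionnaire comes at the end of the use period.

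**App release.** The Results section says "Well Feet app is expected to be published at Google Play and iOS testflight at the end of August 2023". One month of app use is to come after that. The description of the app under Intervention, by contrast, says "The app was made available to download both for iOS and Android".

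**Use of the baseline.** Outcome Measures lists changes in three domains as secondary outcomes: knowledge, self-management and quality of life. Quantitative Analyses tests change within groups by the Wilcoxon signed rank test. Study Design describes a one-month intervention framed by a baseline and an end point. Strengths and Limitations does not mention a delay between baseline and access.

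**The concern.** A pre-post design around a one-month intervention needs a pre value taken close to first exposure. Here the flow ties baseline to enrollment, and the calendar separates enrollment from the app by a month or more. Any change in the waiting weeks, whether from routine clinic care, from having answered the questionnaire once, or from time alone, is counted in the same difference as change under the app. With one arm, nothing in the data separates the two.

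What is at stake is the reading of the secondary outcomes. The Discussion (Principal Findings) expects a pretest-posttest difference in knowledge and links the expected knowledge and behavior results to the app's curriculum and tailoring. It also plans to examine app usage among participants whose knowledge or behavior changed. Someone who changed before having the app would be counted in that group. The waiting time also differs between participants, so the change scores do not all cover the same period.

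**Working it through.** The document prints no baseline-to-end-point interval, so there is no figure of that kind to reproduce. Its calendar can be checked for consistency: release on 31 August plus 30 days gives 30 September, which matches the abstract's completion date.

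**Inputs**
- Baseline date B: 1, 16 or 31 July 2023. Enrollment in July is stated in Results. That baseline falls at enrollment is inferred from the Data Collection flow.
- Release date R: 31 August 2023, with 25 and 28 August as alternative readings of the end of August.
- End point E = R + 30 days.

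**Formulas**
- App-free days: g = R − B
- Total interval: t = E − B = g + 30
- App-free share: g / t

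| Release R | Baseline B | g (days) | t (days) | g / t |
|---|---|---|---|---|
| 31 Aug | 1 Jul | 61 | 91 | 67% |
| 31 Aug | 16 Jul | 46 | 76 | 61% |
| 31 Aug | 31 Jul | 31 | 61 | 51% |
| 28 Aug | 1 Jul | 58 | 88 | 66% |
| 28 Aug | 16 Jul | 43 | 73 | 59% |
| 28 Aug | 31 Jul | 28 | 58 | 48% |
| 25 Aug | 1 Jul | 55 | 85 | 65% |
| 25 Aug | 16 Jul | 40 | 70 | 57% |
| 25 Aug | 31 Jul | 25 | 55 | 45% |

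Over these readings the interval runs from 55 to 91 days, against about 30 days of app use. The app-free share runs from 45% to 67%. For any one release date, the gap differs by up to 30 days between the earliest and the latest July enrollment.

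If the pre value is taken when the link is sent, g = 0, t = 30 and the app-free share is 0%.

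**The case against.** Several points on the other side have force.

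- **The baseline date is inferred.** A reader might conclude that every pre value is known to be 1 to 2 months old. The document does not support that: no completion date is printed, later completion by link is allowed, and the participant-flow figure and the appendix with the secondary outcomes are not available here. This stands, and it limits the claim to most participants. It does not remove the gap, because nothing in the text delays baseline until the app exists.
- **The app may already have been available.** The Intervention section's past tense, taken literally, conflicts with a release still expected. Results gives the only date, and that date fits the abstract's end of data collection, so the check uses it. The two statements need reconciling.
- **At least half of the interval is app-free for everyone.** A reader might infer this, but it depends on release on 31 August. With 25 to 28 August and enrollment on 31 July the share is 45% to 48%.
- **A single arm cannot isolate the app's effect anyway.** True. The delay does not create that weakness; it enlarges it, by adding a month or two in which no app effect is possible.
- **The estimates would feed the later randomized trial.** A reader might infer this too. The abstract's Conclusions speak of refining features and shaping that trial's procedures, and Strengths and Limitations leaves the intervention effect to a further trial. Nothing says that these changes will be carried forward as effect sizes.
- **Mode of completion and the enrollment briefing.** One might argue that tablet versus remote answering, or the briefing itself, shifts scores. The document allows remote completion at baseline, does not fix the mode at the end point, and describes the briefing as covering aims, criteria, procedures and risks. These arguments are speculative and the point does not rely on them.

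**Conclusion.** The point holds at moderate severity and for the secondary change outcomes only. On the article's own dates and flow, most baselines would precede app access by about 1 to 2 months. The tested changes would then cover about 2 to 3 months, roughly half to two-thirds of it without the app. This rests on baseline being answered at or near July enrollment, on release in the last days of August, and on an end point about 30 days later. A participant who answered late by link would have a shorter gap.

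A reader might infer that the study's main result is compromised. It is not: the usability questionnaire and the focus group discussions are collected at the end of the trial and use no baseline. Nor does the article itself call the secondary change a one-month change. That is the natural reading of a baseline and end point placed around a one-month intervention, and it is the reading that the calendar does not support.

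**What to change.** Re-send the existing REDCap questionnaire together with the app link, and use those answers as the pre value. Set the end point at one month from each participant's own link date. The change from July to the link date may be reported descriptively as change without the app, noting that it carries the first retest effect while the later change carries the second. For that reason it is not a clean control period.

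The cost is one extra online questionnaire for each of 40 participants, one more retest exposure and a small amendment, which may have to go to both review boards named under Ethical Considerations. It must be done before the links go out.

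If a repeat is not possible, record and report each participant's baseline-to-link interval. Describe the result as change from enrollment over about 2 to 3 months, not as change over one month of app use, and add the gap to the limitations. In either case, reconcile the two statements about whether the app was already available.
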